### **Study Design**

A three-arm school-based randomized controlled trial (RCT) will be conducted to evaluate the effects of two different kinds of 12-week training programs on the executive function of children with ADHD. The design, conduct, and reporting for the RCT adheres to the guidelines of the Consolidated Standards of Reporting trials (<http://www.consort-statement.org/>) [54]. Participants will be randomly assigned to the GameHIIT group, the GameSAE group, or a non-treatment control group using a random number-producing algorithm (with a 1:1:1 allocation ratio within each school). A stratified random sampling procedure will be conducted that considers gender, IQ, and medication status. Raven's Standard Progressive Matrices (SPM) will be used to measure general intelligence. Equal numbers of boys and girls with similar general intelligence will be included in the three groups. Children taking medication will be equally distributed to the three groups. Participants will not be blinded to treatment allocation because of the intervention nature. To avoid contamination between treatment groups, intervention deliverers will be provided with a list of students in the intervention program. Only those on the list can participate in the intervention. During the 12-week intervention period, participants in the control group will maintain their regular PA levels. For ethical reasons, a cross-over study design will be adopted. That is, participants in the control group will receive either GameHIIT intervention or GameSAE intervention according to their preference after a 12-week formal intervention period. Accordingly, participants in the other two groups will have another 12-week follow up. Therefore, it is expected that all participants in the three groups will benefit from the proposed study. The flow diagram of the study design is shown in **Figure 1**.

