## **(b) (i) Research plan and methodology**

### **Participants**

A total of 42 children with ADHD will be recruited from local schools. The inclusion criteria are: (1) Chinese children aged 8-13 years; (2) a clinical diagnosis of ADHD by developmental pediatricians or clinical psychologists/psychiatrists; (3) a physician/psychologist's recommendation for participation. The exclusion criteria are: (1) diagnosed with a major neurodevelopmental or psychiatric disorders (e.g., autism spectrum disorder, intellectual disability, etc.); (2) acute/chronic diseases that may affect engagement in physical activity; and (3) a tendency to experience convulsions. Informed consent will be obtained from the school principal, parents, and study participants before the study begins. Human research ethics approval will be sought from the Human Research Ethics Committee of the University.

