### **Statistical analyses**

Statistical analyses of the primary and secondary outcomes will be conducted with the IBM SPSS Statistic for Windows, Version 20.0 (2010 SPSS Inc., IBM Company Armonk, NY). Intervention effects for the primary and secondary outcomes will be examined by two-way (trial × time) analysis covariance (ANCOVA), including group as a fixed factor, pre-post intervention difference (change) as the dependent variable, and age, attendance, sports skill, and ADHD symptoms as covariates. Effect sizes (ES) will be presented as partial eta squared values ( $\eta^2$ ). Pairwise comparison will be performed (post-hoc) with Bonferroni correction, with ES presented as Cohen's *d*. Correlational analysis will also be conducted to evaluate the relationship between the changes in executive function and the fNIRS measures. All data will be presented as mean ± SD, and significance will be set as  $p < 0.05$  for all data analysis.

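### The fixed covariate list omits all four factors used to balance the allocation (school, gender, IQ, medication), and the equal numbers stated cannot be guaranteed if those factors are fully crossed

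*Protocol*

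**What the plan says.** Protocol, Participants: "A total of 42 children with ADHD will be recruited from local schools". The number of schools is not given, but the plural implies at least two.

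Protocol, Study Design: three arms are allocated "with a 1:1:1 allocation ratio within each school", which makes school an allocation factor. Three more follow: "A stratified random sampling procedure will be conducted that considers gender, IQ, and medication status". The intended result is then stated: "Equal numbers of boys and girls with similar general intelligence will be included in the three groups", and "Children taking medication will be equally distributed to the three groups".

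Protocol, Statistical analyses: an ANCOVA of the pre-post change, with group as the fixed factor "and age, attendance, sports skill, and ADHD symptoms as covariates". School, gender, IQ and medication are absent.

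The protocol does not state the IQ cut-points, the block size, whether the factors are crossed, or whether children are randomised one at a time or as a complete list. Such details may sit in a randomisation plan or SAP, and their absence is not the point here. The covariate list is different, because the protocol itself fixes it.

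**The concern.** Forcing balance on a prognostic factor removes that factor's contribution to the difference between arms. A model that omits the factor still counts its contribution as residual noise, so the standard error is too large for the design used. The test then rejects too rarely under the null and loses power.

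Where balance is not fully achieved, the same omission leaves the remaining imbalance in the estimate. With 14 children per arm (42/3), a difference of 3 medicated children between two arms is 3/14 = 21 percentage points. If medication shifted the change score by 0.5 SD (assumed), the comparison would move by 0.21 × 0.5 = 0.11 SD. Adjustment deals with both cases.

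The second issue is feasibility. Four crossed factors may be more than 42 children in three arms can fill, and the protocol states equality as a fact.

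**Working it through.** **The plan's own figure.** Three groups of 10 completers with 30% loss: 30/0.7 = 42.9, which agrees with the stated total of about 42.

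**Cross-check of the two sections.**

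| Factor | Used in allocation | In the model |
|---|---|---|
| School, gender, IQ, medication | yes | no |
| Age, attendance, sports skill, ADHD symptoms | no | yes |

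The lists do not overlap. This needs no assumption.

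**Size of the analysis effect.** Assumed: permuted blocks of 3 in fully crossed strata, IQ in two levels, no other covariates in the model.

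With 3 schools and no dropout, the unadjusted three-arm test rejects a true null in 3.5% of trials when the factors explain 20% of variance. When they explain 30%, repeated simulations gave 2.0% and 2.5%. The adjusted test rejects in about 5%.

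A second set used 30% loss, 75% boys, 50% on medication, residual SD 1, and, for power, both active arms 1.2 SD above control (4,000 runs each):

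| Schools | Shift per factor | Error: none / all four | Power: none / three child factors / all four |
|---|---|---|---|
| 2 | 0 | 0.057 / 0.054 | 0.72 / 0.69 / 0.68 |
| 2 | 0.5 SD | 0.040 / 0.051 | 0.63 / 0.68 / 0.68 |
| 2 | 1.0 SD | 0.023 / 0.050 | 0.43 / 0.63 / 0.67 |
| 4 | 0 | 0.048 / 0.043 | 0.72 / 0.68 / 0.63 |
| 4 | 0.5 SD | 0.039 / 0.052 | 0.63 / 0.65 / 0.63 |
| 4 | 1.0 SD | 0.033 / 0.055 | 0.42 / 0.60 / 0.63 |

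The simulation standard error is about √(0.05 × 0.95/4000) = 0.003 for the error rate and √(0.65 × 0.35/4000) = 0.008 for power.

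To place these shifts on the variance scale: gender contributes 0.75 × 0.25 = 0.1875 and IQ and medication 0.25 each, in total 0.6875. At 0.5 SD the share is (0.25 × 0.6875)/(1 + 0.25 × 0.6875) = 15%. At 1.0 SD it is 0.6875/1.6875 = 41%. School effects come on top. The 0.5 SD rows are therefore the realistic ones, and the 1.0 SD rows lie beyond the 20% to 30% range.

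**Stratum count.** Strata = 2 (gender) × 2 (IQ) × 2 (medication) × S (schools):

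| S | Strata | Children per stratum |
|---|---|---|
| 2 | 16 | 42/16 = 2.6 |
| 3 | 24 | 42/24 = 1.75 |
| 4 | 32 | 42/32 = 1.3 |
| 6 | 48 | 42/48 = 0.9 |

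At S = 2 there are 16 × 3 = 48 stratum-by-arm cells for 42 children, so not every stratum can hold one child per arm.

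**What that does to balance.** Mean difference between the highest and lowest arm in number of boys / higher-IQ / medicated children:

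| S | Crossed blocks of 3 | No stratification | Arm sizes differ by 4 or more (crossed) |
|---|---|---|---|
| 2 | 2.2 / 2.2 / 2.2 | 2.7 / 3.1 / 3.2 | 36% |
| 4 | 3.2 / 3.0 / 3.0 | 2.7 / 3.1 / 3.1 | 56% |
| 6 | 3.9 / 3.3 / 3.4 | 2.7 / 3.1 / 3.1 | 65% |

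Stratification helps with 2 schools, has essentially no benefit left at 4, and is worse than none at 6.

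**The case against.** **The outcome is a change score.** Differencing removes stable effects of IQ, gender, school and continuing medication, and nothing in the protocol shows that these factors explain 20% to 30% of the variance of change. Age and ADHD symptoms are already covariates and may overlap with medication. This stands: the benefit of adjusting is conditional, and with no prognostic value adjustment costs power. With 4 schools at 0.5 SD, adjusting for all four factors gains nothing visible.

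**A larger error shift.** A reader might take the standard-error ratio 1/√(1 − R²), which is 1.118 or 1.195 for R² of 20% or 30%, and conclude that the true error is 2.8% or 1.9%. That formula needs perfect balance on all four factors, which sparse strata do not give. The simulated values are the ones to use.

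**False positives.** A reader might infer that the omission inflates type I error. It does not; the direction is conservative.

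**Failed promises.** A reader might say that the plan promises precision, or that its balance will not be delivered. The protocol promises balance only. Whether balance fails depends on the number of schools, IQ cut, crossing and block size, none of which is stated.

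**Hand adjustment.** It is tempting to say that equal numbers could be reached only by adjusting the list by hand, which would make allocation predictable. The documents do not support this. If children are assessed first and randomised together, a computer can draw from balanced allocations. Random 14/14/14 draws with gender, IQ band and medication within 1 across arms (school unconstrained) were found every time.

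What the objections leave untouched is the mismatch between the allocation factors and a covariate list that the protocol itself fixes.

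**Conclusion.** The point holds in a limited form. The mismatch is plain from the text and rests on no assumption.

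Its consequence is conditional. If the factors predict the change in executive function, the test runs at about 2% to 4% instead of 5% (assumed: 20% to 30% of variance explained, 2 to 4 schools, crossed blocks of 3). With 2 schools, 0.5 SD effects and 30% loss, power is about 5 points lower than it need be (0.63 against 0.68). Chance imbalance in medication or IQ would also go uncorrected. If the factors are not prognostic, adjusting for the three child-level factors costs about 4 points (0.72 to 0.68 or 0.69). Adding school costs about 1 further point with 2 schools and about 5 with 4 (0.68 to 0.63).

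The secondary point is conditional on full crossing: equal numbers cannot be guaranteed with 2 or more schools. That does not show that balance will be poor. No finding of invalid inference or predictable allocation follows.

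**What to change.** **Model.** Add gender, medication status and baseline IQ (Raven's score, continuous). Add school if the number of schools is small. Drop attendance: it is measured after randomisation and does not exist for controls in the 12-week comparison.

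Degrees of freedom, with 30 completers and one parameter per covariate: the present model uses 1 + 2 + 4 = 7 parameters and leaves 23. Adding three and dropping one leaves 30 − 9 = 21. School takes S − 1 more, so 20 remain with 2 schools and 18 with 4.

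**Allocation.** Use computer minimisation with a random element, or a computer-constrained allocation of the complete list, over school, gender, medication and IQ band. State the factors and their levels.

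**Wording.** Replace the statements of equal numbers with approximate balance, and call the procedure stratified randomisation, since it concerns allocation and not sampling.

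The cost is a protocol wording change, a minimisation or constrained-allocation program, and a few residual degrees of freedom. If the factors turn out not to be prognostic, it also costs the roughly 4 power points given above. The change should be made before allocation begins.

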## **Intervention Protocols**

In the GameHIIT group, a specially designed game-based training program with HIIT in nature will be delivered to the participants for 12 weeks. A small-sided games (SSGs) approach in rugby will be adopted in this intervention program as it is effective in developing physical and technical capabilities in children, and provides similar physical stimulus, regardless of the experience of the children. Importantly, rugby has been introduced in a large scale to primary and secondary schools in Hong Kong. There will be two training sessions each week. In each training session, there will be four sets of training programs separated by 3 minutes of passive recovery in accordance with a previous study. Each set of activities will last for around 5 minutes; therefore, the total duration of each training session will be approximately 30 minutes. A brief description of the proposed training program is given in **Table 1**. A small group size (4-6 children per group) will be adopted to facilitate individual supervision and adaption of the exercise program. Also, certain social, cognitive and coordinative elements will be included which may play an important role in liking the neuropsychological concept of executive function. All the training programs will be organized for participants after school hours. A qualified rugby coach will be hired to implement the rugby training program. To encourage maintenance of an appropriate level of exercise intensity, participants will be fitted with heart rate monitors (Polar H7), which will be connected to a central iPad application (Polar Team). The coach will be able to view real-time HR data during training. If necessary, we will adjust the exercise intensity to ensure that HR can reach the target HR zone. Adherence to the designed GameHIIT protocol will be recorded by the coach in each training session.

In the GameSAE group, participants will attend a tailor-made game-based exercise training program designed by one of our group members. Similar to GameHIIT, the intervention will comprise 12 weeks of structured aerobic exercise sessions, lasting one hour on average in each session and up to twice per week. Six to eight stations of multidimensional exercises will be set up for each session. Adopting the train-the-trainer (TTT) model, training will be provided by front-line healthcare providers who are mainly social workers. Children will be instructed to finish the exercises in all stations one after another in a predetermined order. The exercise program has 3 stages and each of the stage last around four weeks. In the first stage, the aim is to build trust to their coaches, and paired group activities are included. In the second stage, the exercise intensity will be increased to promote cardiopulmonary endurance and muscular strength. In the final stage, the exercise intensity for each session will be higher than that of the previous stages and there will be large group activities as well. To record the progress of the training classes and provide feedback to the front-line healthcare providers, a professional coach and research assistant will take part in the training once every two weeks.

## **Outcomes Measurements**

Before (T0) and after (T1) the 12-week intervention period, as well as another 12-week follow up (T2), several different indicators will be recorded, including executive function, cerebral hemodynamic response, weekly PA levels, physical fitness, feeling state, and enjoyment and adherence to the intervention. All assessments will be conducted by trained research staff blinded to group allocation. To ensure the accuracy and consistency of the measurements, a measurement training session and protocol manual, including specific instructions for

conducting all assessments, will be provided to the research staff. A senior researcher will be present during all the testing sessions. All physical assessments will be conducted in a sensitive manner (e.g., weight/waist circumference will be measured in a private setting), and the cognitive function tests and questionnaires will be completed under exam-like conditions. Also, participants will be instructed to follow similar diets on the main trial days. Only distilled water will be allowed before the tests in the main trials.

## **Primary Outcome**

### **Executive Function**

Executive function will be assessed using a battery of tests on a laptop computer that will take approximately five minutes to complete. The battery of tests include the Colour-Word Stroop Test (CWST) and Eriksen Flanker Test (EFT) which are classic tasks that measure inhibition response, one of important components of executive function. Previous studies have reported medium to large effect size of the different exercise intervention programs on inhibition of children and adolescents with ADHD [27, 28, 40]. In these two tests, both reaction time and response accuracy will be recorded and analyzed. This battery has been used previously by research group members to investigate the effect of exercise on cognition in young people [59]. The instructions for each test will be provided to the participants and they will be allowed to ask questions for clarification. Participants will be familiarized with the testing battery seven days prior to the main trial, and each test will start with 3-6 practice stimuli to re-familiarize participants with the task at hand and eliminate any potential learning effects. In the main trial, participants will complete the tests in a group of 3-4 participants. They must remain silent from the other participants so that they cannot interact with others while taking the tests.

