Therefore, the primary aim of the proposed study is to investigate the effect of two different kinds of exercise programs, i.e., a 12-week game-based HIIT (GameHIIT) program and a 12-week game-based structured aerobic exercise (GameSAE) program, on the executive function of children with ADHD. The secondary aim is to explore a possible mechanism behind the potential association between exercise intervention and improvements in executive function. The hypothesis of the proposed study is that both GameHIIT and GameSAE programs will significantly improve the executive function of children with ADHD, compared with those in the control group. A secondary hypothesis is that the GameHIIT group may confer additional benefits when compared with the GameSAE group.

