### **Sample Size Calculation**

The sample size is calculated using G\*Power 3.1. To elucidate the differences in the executive function tests with a statistical power of 0.9, a conservative effect size of 0.65 based on a previous systematic review with the average effect size calculated regarding the effect of exercise on executive function in children with ADHD [24], a two-tailed alpha level of 0.05, it is determined that 10 participants per group will provide adequate power to detect statistically significant differences. Assuming a 30% loss in the intervention, we will need to approach about 42 eligible participants to achieve the planned sample.

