### **Cerebral Hemodynamic Response**

Accompanied by the executive function test, the cortical hemodynamic response in the prefrontal cortex will also be recorded using a multi-channel fNIRS (Octamon fNIRS system, Artinis, Netherland) applying two wavelengths of near-infrared light (785 and 830 nm). The device consists of eight light sources and two detectors secured onto a head cap. The device will be placed over the left and right prefrontal cortex according to the guidelines in the handbook provided by the manufacturer. The data will be analyzed as described [60].

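### At least four executive-function measures are listed as primary, each tested at 0.05, and the protocol does not say which measure or combination decides success

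*Protocol*

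**What the plan says.** The Executive Function section, under Primary Outcome, describes a battery that includes the Colour-Word Stroop Test and the Eriksen Flanker Test, and adds: "In these two tests, both reaction time and response accuracy will be recorded and analyzed". Two tests with two scores each give at least four measures.

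The next section, Cerebral Hemodynamic Response, stands under the same main heading, ahead of Secondary Outcomes: "Accompanied by the executive function test, the cortical hemodynamic response in the prefrontal cortex will also be recorded". The Background, however, treats mechanism as a lower-order question: "The secondary aim is to explore a possible mechanism behind the potential association between exercise intervention and improvements in executive function".

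Statistical analyses applies the same ANCOVA to all primary and secondary outcomes and states that "significance will be set as $p < 0.05$ for all data analysis". The only multiplicity correction is Bonferroni for the post-hoc comparisons between pairs of groups.

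The hypothesis in the Background is that both programs improve executive function relative to control. Neither it nor the Sample Size Calculation names a measure.

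**The concern.** The Bonferroni step works between groups within one measure. It does nothing about having four measures. A protocol with four primary measures needs one of three things: a lead measure, a correction across measures, or a rule that all must succeed. This one has none of them, and it fixes 0.05 for every analysis.

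Two things are at stake. First, the stated 5% level need not be the error rate of the claim that exercise improved executive function. Second, the claim could rest on whichever score turns out favourable. Reaction time and accuracy can move in opposite directions, so a group that became faster but less accurate could be reported as improved. With 10 completers per group planned, chance differences on single scores will be large.

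**Working it through.** **Inputs from the protocol.** Three arms with 1:1:1 allocation (Study Design); 10 completers per group (Sample Size Calculation); at least 2 tests × 2 scores = 4 measures (Executive Function); 0.05 per analysis, with Bonferroni over the three group pairs (Statistical analyses).

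**Assumptions.** The protocol gives no correlation between the measures, so I use 0, 0.5, 0.7 and 0.9, equal for all pairs. No covariates are included. All results are under the global null (no program affects any measure), from 60,000 simulated trials of 3 × 10 children.

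**The plan's own level.** For a single measure, the simulated chance of a significant omnibus group effect is 5.0-5.1%, which reproduces the stated 5%. The protocol gives no error rate across measures to compare with.

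**Four independent measures, by formula.** 1 − 0.95^4 = 1 − 0.8145 = 0.1855, or 18.5%.

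**Four measures, by success rule.** Each pairwise comparison uses the two-sided Bonferroni critical value, which leaves 0.05/6 in each tail, with 27 degrees of freedom.

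| What counts as success | One measure | Four, corr. 0 | 0.5 | 0.7 | 0.9 |
|---|---|---|---|---|---|
| Omnibus group effect on any measure | 5% | 18.6% | 16.0% | 13.6% | 9.8% |
| The same, plus any significant pair on that measure | 4.2% | 15.7% | 13.7% | 11.7% | 8.4% |
| At least one program better than control on any measure | 1.5% | 6.0% | 5.2% | 4.5% | 3.2% |
| Both programs better than control on the same measure | 0.11% | 0.46% | 0.49% | 0.45% | 0.31% |

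The second row shows that the existing Bonferroni step removes little of the inflation when a difference between any two groups counts.

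**A limit of the last row.** It assumes that both programs are inert. If one program truly works on every measure, a false claim for both needs only the other to beat control by chance. That chance is at most 4 × 0.05/6 = 3.3%, against 0.05/6 = 0.83% for one measure.

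**Cost of correcting across four measures.** The first Holm step is 0.05/4 = 0.0125. Used for all four independent tests, that level gives 1 − (1 − 0.0125)^4 = 4.9%. The planning effect size is 0.65, with no metric stated.
- Read as Cohen's f in a three-group ANOVA with 30 completers, power falls from 86% at 0.05 to 68% at 0.0125. The total needed for 90% power rises from 36 to 45.
- Read as Cohen's d between two groups of 10, power falls from 28% to 12%. The number per arm for 90% power rises from 51 to 70.

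Neither reading returns the protocol's 10 per group at 90% power. That is a separate matter, and nothing here depends on it.

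**The case against.** The strongest counter-argument is that the protocol never says one significant score out of four is enough. Its hypothesis is directional and joint: both programs, each against control. On that reading the false-positive chance under the global null is about 0.5% or less, well inside 5%. This stands. A reader might infer that the chance of a false primary claim is far above 5% whatever the rule, but that is true only if any significant group effect counts. What remains is that the protocol does not commit to the joint reading either, and four measures raise the error above that of one measure on every reading.

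A reader might also add the fNIRS signals to the count and arrive at a much higher figure. The documents do not support that. They do not fix how many fNIRS signals will be tested, mechanism is the secondary aim, and a haemoglobin signal cannot by itself support a claim about executive function. What is left is a contradiction between the heading and the stated aim.

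A statistical analysis plan, not shown here, might add a multiplicity rule. But the protocol does more than stay silent: it sets 0.05 for all analyses and confines correction to group pairs. A later correction across measures would change that statement rather than fill in detail.

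Finally, naming a single score does not by itself prevent faster but less accurate responding from counting as success. If that score were reaction time, the pattern would still pass. The fix has to deal with this.

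**Conclusion.** The point holds. At least four measures are primary, each is tested at 0.05, and nothing says which measure or combination decides. The size of the problem depends on a success rule that the protocol leaves open:
- about 10-19% instead of 5% if any group effect counts (correlation 0.9 down to 0);
- about 3-6% against 1.5% if at least one program must beat control;
- about 0.5% or less if both must do so on the same measure.

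These figures rest on the global null, 10 completers per group, equal correlations and no covariates. The defect is that the plan does not determine which of them applies. The placement of cerebral hemodynamic response under Primary Outcome conflicts with the stated aims but adds no error figure of its own.

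**What to change.** Make the choice before any outcome data are examined. Waiting until data lock would be too late: participants know their allocation and the protocol describes no blinding of analysts, so results could be seen before then.

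- **Preferred:** name one primary measure and make the others secondary. It should preferably combine speed and accuracy. Otherwise, use one reaction-time score that counts as success only if accuracy is not worse, with ‘not worse’ defined in advance. State alongside it which group comparison decides success.
- **Alternative:** keep all four and apply Holm across them, with the Bonferroni pairwise step inside each measure as now. This alone does not settle the trade-off between speed and accuracy, so the same accuracy condition is needed for the reaction-time scores.
- **In either case:** move cerebral hemodynamic response to Secondary Outcomes, in line with the secondary aim.

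The preferred option is a change of wording. It needs no correction across measures and no extra children on that account, but it narrows the headline claim, and an accuracy condition may cost some power. Holm costs more: with 0.65 read as Cohen's f and 30 completers, power falls from about 86% to 68% at its first step. In a trial of this size that favours the single measure.
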